**Exclusion criteria**
1. Acute coronary syndrome 2. Anuria in the first 2 h after admission 3. Sepsis 4. Consciousness impairment 5. Pregnant or breastfeeding women 6. Severe valvular heart diseases (severe valvular stenosis or regurgitation) 7. Admission sodium level >140 mEq/L 8. Serum total bilirubin > 3mg/dL 9. Serum potassium >5.5 mmol/L 10. Allergy or contraindication to tolvaptan 11. Emergency indication for hemodialysis 12. Cardiogenic shock or mechanical circulation support

* *The wet-warm phenotype is defined as a patient with ≥2 clinical signs of congestion (bibasilar rales, bilateral ankle edema, ascites, jugular venous distension) and N-terminal pro B-type natriuretic peptide (NT-proBNP) at admission ≥900 pg/ml*.

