### Statistical Consideration

#### Sample Size

In the REALITY-AHF dataset (*n* = 1682) (15), we identified and retrieved the records of the patients treated with an intravenous furosemide within 30 min of emergency department visits. Using the ESC Heart Failure Association definition (<150 ml urine output/h), we identified 95 patients with diuretic resistance in the first 90 min, while their urine output within 48 h was 3,896 ± 1,595 ml. Assuming that the add-on tolvaptan therapy could yield 1,000 ml more urine output at 48 h, we calculated the sample size of 128 patients with an enrollment ratio of 1:1 after adjusting for 15% dropout during the follow-up period. This sample size was intended to provide a 90% power and 0.05 type I error probability.

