#### Statistical Methodology

The intention-to-treat the population, which included all randomized patients to whom at least one dose of tolvaptan was administered, will be analyzed for the primary and secondary endpoints. As an exploratory analysis, we will evaluate interactions between tolvaptan add-on treatment and pre-specified subgroups on primary and secondary outcomes. Subgroups were defined for age (age > 65 and ≤ 65), eGFR at admission (eGFR 15–29 and eGFR 30–60), sodium and chloride levels at admission (above or below median), furosemide-naive or not, diuretic response achieved in the first 2 h after initial intravenous injection, blood urea nitrogen/creatinine (above or below median), and left ventricular ejection fraction ≤ 40 or >40%. A *P*-value of < 0.05 was considered statistically significant. Continuous variables are expressed as mean ± standard deviation if normally distributed or as median (interquartile range) if otherwise. When necessary, the variables were transformed for further analysis. Statistical significance was defined as two-sided 5%, and all analyses were performed using IBM SPSS^®^ (version 24.0) and R version 3.5.2 (R Foundation for Statistical Computing, Vienna, Austria; ISBN 3-900051-07-0, URL http://www.R-project.org). Normality was assessed using the Shapiro-Wilk test. The independent Student's *t*-test or Mann-Whitney U test was used to compare the two treatment groups according to each parameter. Categorical data will be displayed as a percentage or number and compared using Fisher's exact test. The relationship between baseline characteristics and outcomes will be compared by one-way analysis of variance, Kruskal-Wallis test, or χ^2^ test, as appropriate.

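### Exploratory interactions with sodium, chloride and BUN/creatinine rest on median splits; one pre-specified linear interaction per marker would be a stronger test at almost no cost

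*Protocol article*

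**What the plan says.** The Statistical Methodology section of the protocol article announces the subgroup work in these terms: "As an exploratory analysis, we will evaluate interactions between tolvaptan add-on treatment and pre-specified subgroups on primary and secondary outcomes".

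Three continuous admission markers enter as two-level subgroups. Two are covered by "sodium and chloride levels at admission (above or below median" and the third by "blood urea nitrogen/creatinine (above or below median". No numeric value or external source for the median is given, so it is presumably the median of the trial's own patients.

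Other subgroups in the same sentence have numeric cuts fixed in advance: "age (age > 65 and ≤ 65), eGFR at admission (eGFR 15–29 and eGFR 30–60", and LVEF at 40%. No analysis that keeps sodium, chloride or BUN/creatinine continuous is described. Significance is judged at a two-sided 5% level.

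**The concern.** The interaction analyses ask which diuretic-resistant patients gain more, or less, from adding tolvaptan. If that gain changes gradually with sodium, chloride or BUN/creatinine, a two-level split treats a patient just above the median like one far above it, and separates two near-identical patients on either side of it. Some of the information already collected goes unused, in a trial of 128 patients where interaction power is limited to begin with.

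The cut-point also has drawbacks. It is known only after enrolment, it varies from sample to sample, and nothing in the article gives it clinical meaning. For sodium it describes a truncated population, because entry excludes "Admission sodium level >140 mEq/L". The above-or-below wording does not say where a patient exactly at the median belongs, which matters if sodium is reported in whole mEq/L.

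At stake is the usefulness of the exploratory findings, not the trial's main result.

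**Working it through.** **Inputs from the article (Sample Size).** SD 1,595 ml ("their urine output within 48 h was 3,896 ± 1,595 ml"), assumed difference 1,000 ml, 90% power, two-sided 0.05, 1:1 allocation, 15% dropout, total 128.

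**The plan's own figure.** Per arm, n = 2 × (1.960 + 1.282)² × (1,595/1,000)² = 53.5, rounded up to 54, so 108 in total. Then 108/0.85 = 127.1, rounded up to 128. The stated figure is reproduced, and about 108 patients are expected to be evaluable.

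**Information kept by a median split.** For a linear interaction, the share kept is the squared correlation between the marker and its above-median indicator. For a normal marker this is 2/π = 0.637, a loss of 36.3%. In information terms 108 patients act like 108 × 0.637 = 69, and 128 like 81.

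**Power.** For 80% power the standardized effect must be 1.960 + 0.842 = 2.80. After the split it is 2.80 × √0.637 = 2.235, and power is Φ(2.235 − 1.960) = 61%. Simulation of the two interaction tests at 108 and 128 patients gave 77% continuous against 56% to 57% split.

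**Detectable interaction.** With 1,595 ml taken as the residual SD, the continuous interaction per SD of the marker has SE = 2 × 1,595/√n. The detectable size is 2.80 × SE, divided by √0.637 = 0.798 for the split.

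| Patients | SE (ml per SD) | Detectable, continuous | Detectable, split |
|---|---|---|---|
| 108 | 307 | 860 | 1,080 |
| 128 | 282 | 790 | 990 |

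On the split scale, the difference in effect between halves has SE = 4 × 1,595/√n, which is 614 ml at 108 and 564 ml at 128. Power to detect a 1,000 ml difference between halves, as large as the whole assumed treatment effect, is Φ(1,000/614 − 1.960) = 37% at 108 and 43% at 128.

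**Smaller interactions (assumed sizes, n = 108, both tails counted).** At 300 ml per SD, power is 16% continuous and 12% split. At 200 ml per SD it is 10% and 8%.

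**Sensitivity to the marker's distribution.** The article gives no distributions, so these are assumptions, each with an interaction linear on the raw scale:

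| Assumed marker | Loss from the split |
|---|---|
| Uniform | 25% |
| Sodium cut off above 140 (mean 134–140, SD 4–5) | 34–38% |
| Same, whole mEq/L with ties at the median | 32–42% |
| Normal | 36% |
| Lognormal, log-SD 0.3–0.6 (plausible for BUN/creatinine) | 41–53% |
| Any, if the true effect is a step at the median | none |

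In the whole-number sodium cases, 9% to 15% of patients sit exactly at the median. For a normal marker the sample median has a standard error of 0.11 SD at 128 patients and 0.12 SD at 108.

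**The case against.** The other side has a fair case. The analysis is labelled exploratory, the subgroups are named in advance, median splits are common, and an article may leave the interaction model to an analysis plan that is not shown. That keeps the severity low. It does not remove the point: the article does fix how these three markers are formed, and a two-level form limits any model built on it.

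The size of the loss depends on assumptions about distribution and shape that the article cannot confirm. That stands, which is why a range is given. For small interactions neither analysis is informative, and changing the model does not rescue them. That also stands.

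The gain can be given back. If the truth is linear with 80% power on 1 df, a flexible interaction test has about 71% power on 2 df and 64% on 3 df, against 61% for the split. Choosing between a line and a spline after seeing outcomes would be worse practice than a median fixed by rule. So the continuous form must be set in advance.

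A reader might also infer three stronger things that the document does not support:

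- **That the cut-points are tuned to the results.** They depend on baseline values, not outcomes. The rule is pre-specified and does not in itself inflate type I error.
- **That a median cut can never be used elsewhere.** A reported numeric median can be applied to another cohort; it is arbitrary rather than untransferable.
- **That 36% is lost whatever the data look like.** It is the figure for a normal marker and a linear interaction.

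**Conclusion.** The point holds as a cheap improvement of low severity. For a graded interaction, the stated method is weaker than one that uses the same data. With a roughly normal marker and a linear interaction, about 36% of the information is lost, and 80% power becomes about 61%. In absolute terms the rise in the detectable interaction, from about 860 to about 1,080 ml per SD, assumes 108 evaluable patients and a residual SD equal to the planning SD.

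That the median comes from the trial sample is an inference from the absence of any other value.

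Nothing here touches the primary comparison, the sample size of 128 or the type I error of the trial, and it would be wrong to read it as invalidating the subgroup analyses.

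**What to change.** For each of sodium, chloride and BUN/creatinine, pre-specify one model with treatment, the marker as a continuous variable and their product, and make the 1 df product term the interaction test. Decide before outcomes are seen whether BUN/creatinine is log-transformed for skewness. Use a spline only as a pre-specified sensitivity check, or to plot the treatment effect with its 95% CI across the marker's range.

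Keep the above/below-median estimates for display. Report the numeric median, and state which group takes values equal to it.

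The same change could be applied to age, eGFR and LVEF, which are also dichotomized, though at fixed cuts.

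Cost: an assumed linear shape and a few extra model lines in R, which the article already names. No further data are needed.

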**Inclusion criteria**
1. Aged 20–75 years 2. Admitted to hospital with a primary diagnosis of acute heart failure with wet-warm phenotype^*^ 3. Cumulative urine volume output <300 mL within 2 h after the first dose of intravenous furosemide 4. eGFR at admission 15–60 mL/min/1.73 m^2^

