### Endpoints

The primary endpoint was the cumulative urine output at 48 h after randomization. The secondary endpoints include the improvement of fractional excretion of sodium at 6 h, total dose of furosemide, changes in the body weight, net fluid loss, improvement of dyspnea by the 7-point Likert scale, reduction of diastolic dysfunction parameters on echocardiography, incidence of clinically relevant WRF, and changes of NT-proBNP at 48 h. Clinically relevant WRF is defined as an increase in serum creatinine level ≥0.3 mg/dl within 48 h accompanied by the doubling of furosemide dose according to the diuretic treatment protocol. A summary of the study endpoints is shown in Appendix 3.

Safety will be assessed based on the adverse effects reported throughout the study with vital signs, physical examination, clinical laboratory tests, and 12 lead-electrocardiogram. Safety topics of special interest include severe hypernatremia (plasma sodium increase > 12 mEq/24 h), hypokalemia, and hepatic injury (elevation of AST and/or ALT > three-fold the upper limit of the normal). Adverse effects and laboratory abnormalities were compared between the two treatment groups.

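### The primary test and effect measure for 48-h urine output are left to the data, and baseline variables known at randomization stay out of the treatment comparison

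*Protocol article*

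**What the plan says.** All references are to the Protocol article.

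- **Endpoint.** Endpoints: "The primary endpoint was the cumulative urine output at 48 h after randomization".
- **Test.** Statistical Methodology: "Normality was assessed using the Shapiro-Wilk test". The next sentence says that Student's t-test "or Mann-Whitney U test was used to compare the two treatment groups according to each parameter". The primary endpoint gets no separate treatment.
- **Transformation.** Same section: "When necessary, the variables were transformed for further analysis". No criterion is given.
- **Sizing.** Sample Size assumes 1,000 ml more urine with tolvaptan, against a reference of 3,896 ± 1,595 ml in 95 patients from an earlier dataset. It then states: "This sample size was intended to provide a 90% power and 0.05 type I error probability". Statistical Methodology makes the 5% level two-sided.
- **Baseline data.** Table 1 requires "Cumulative urine volume output <300 mL within 2 h after the first dose of intravenous furosemide" and an admission eGFR of 15–60. Study Flow and Loop Diuretic Strategy bases the starting furosemide dose on prior oral use and places randomization 2 h after that dose, so these facts are known before allocation. Statistical Methodology uses eGFR, furosemide-naive status and 2-h response for exploratory subgroup interactions, and plans separate tests of baseline characteristics against outcomes. Neither adjusts the treatment effect.

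**The concern.** The three analyses that the text allows do not answer the same question. The t-test compares means in ml. The Mann-Whitney test compares ranks and gives no ml estimate unless one is added, and the article adds none. A t-test on a log scale, one possible transformation, would compare ratios. Only the first matches the quantity used for sizing. If the data lead to another branch, the article's own convention would also report medians, and the planned mean difference might never be shown.

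The choice would be made on the trial's own outcome data, by staff who can know the allocation. The text does not say whether normality is checked per arm or pooled, or when a transformation takes precedence over the rank test. Two analysts could follow it in good faith and report different primary results.

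Separately, early urine response, eGFR and prior diuretic use plausibly predict later urine output, and the article itself treats them as relevant by naming them as subgroups. Leaving them out of the main comparison gives up whatever precision they carry.

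**Working it through.** **1. Reproduce the stated sample size.** Inputs from Sample Size: difference 1,000 ml, SD 1,595 ml, power 90%, two-sided alpha 0.05, 1:1 allocation, 15% dropout.

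n per arm = 2 × (1.960 + 1.282)² × 1,595² / 1,000² ≈ 53.5, so 54 per arm and 108 in total.

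Dropout: 108 / 0.85 = 127.1, rounded up to **128**. This matches the article. The design is therefore an unadjusted comparison of two means in ml.

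**2. How the pre-test rule behaves.** The article does not give the shape of the outcome distribution, so three shapes with mean 3,896 and SD 1,595 were assumed. Each scenario had 54 per arm and 6,000 simulated trials, with either no effect or a pure 1,000 ml shift. The t-test was used if Shapiro-Wilk did not reject at 5% in either arm, and Mann-Whitney otherwise. That is one reading of the text.

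| | Normal | Gamma | Lognormal |
|---|---|---|---|
| t-test selected | about 90% | about 20% | 3–4% |
| Type I error, rule as written | 4.5% | 5.5% | 5.0% |
| Type I error, smaller of the two p-values | 5.2% | 6.5% | 6.6% |
| Power, t-test always | 90.0% | 89.1% | 89.5% |
| Power, rule as written | 89.7% | 91.0% | 95.0% |
| The two tests disagree on significance (1,000 ml shift) | 3.4% | 4.7% | 6.1% |

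The rule holds its level and does not cost power. What varies is which test, and so which quantity, becomes primary.

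**3. What adjustment could gain.** With the share R² of outcome variance explained by the covariates, the residual SD is 1,595 × √(1 − R²). The standard error of the difference is that SD × √(2/54), and power follows from the non-central t distribution at two-sided 5%. R² is an assumption, because the article gives none.

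| R² | Residual SD (ml) | SE (ml) | Power |
|---|---|---|---|
| 0 | 1,595 | 307 | 89.8% |
| 0.10 | 1,513 | 291 | 92.5% |
| 0.25 | 1,381 | 266 | 96.1% |

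The SE falls by 1 − √0.90 = 5% and by 1 − √0.75 = 13%.

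**The case against.** **An unadjusted test is valid, and an article may leave a covariate model to the full protocol or SAP.** Both are true. Absence of adjustment alone would be no error, and the sizing is consistent with an unadjusted test. What stands is that the article does state a rule for comparing the arms, and that rule leaves the primary test open. A SAP that names one model would have to override it.

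**The link from Shapiro-Wilk to the choice of test is only implied.** It rests on adjacent sentences, and the transformation sentence follows one on descriptive statistics without naming the primary endpoint. This is fair. But if no link was meant, the choice is less constrained, not more.

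**Skewness is assumed.** Agreed. The reference output is given as mean ± SD, the format that the article reserves for normally distributed variables, and 3,896 − 2 × 1,595 = 706 ml is still positive. If output is normal, the t-test is chosen about nine times in ten. A reader might infer that the rank test will usually be primary; the documents do not show that.

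**No false-positive inflation follows from the text.** Agreed. A reader might infer an error rate of about 7%. Simulated figures of 6.2% to 7.3% arise only if someone runs t, Mann-Whitney and log-t and reports whichever is significant. The article describes no such practice and never names a log-t test.

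**The baseline data are not discarded, and the gain may be small.** Both stand. The variables are used in exploratory subgroup and association analyses. Eligibility also narrows 2-h output (below 300 ml, anuria excluded) and eGFR (15–60), which would tend to weaken their correlation with outcome. The first intravenous furosemide dose is described as a dosing rule and is not listed under Measurements.

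**Conclusion.** The point holds in a limited form. The article does not fix one test and one effect measure for its primary endpoint, in an open-label trial sized on a mean difference in ml. A rank or transformed analysis would not estimate that difference.

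The rule as written is valid, with type I error of 4.5% to 5.5% and no loss of power under the three assumed shapes. The harm is an unfixed estimand, scope for analyst choice (the two tests disagree in about 3% to 6% of simulated trials with a 1,000 ml shift) and forgone precision. That precision is worth 0 to about 6 points of power for an assumed R² of 0 to 0.25 (96.1 − 89.8 = 6.3).

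The documents support neither a claim of inflated error nor a claim that the trial is underpowered for this reason. It is an inexpensive improvement that should be made before analysis.

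**What to change.** For the primary endpoint:

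- Pre-specify a linear model (ANCOVA) of 48-h urine output in ml on arm, 2-h urine output as a continuous variable, admission eGFR and prior loop-diuretic use, with heteroscedasticity-robust standard errors. Add the first intravenous furosemide dose if it is recorded.
- Report the adjusted mean difference in ml with its 95% CI.
- Remove the normality check and the open transformation option for this endpoint, and keep Mann-Whitney as a sensitivity analysis.

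For change endpoints with a baseline value (fractional excretion of sodium, NT-proBNP on the log scale, echocardiographic parameters), adjust for that baseline.

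If a SAP already fixes one primary model, it is enough to say that it supersedes the article's wording. The cost is a change of analysis text. The main covariates are already needed for eligibility or treatment, and no extra patients or visits are required. Only the recording of the first intravenous dose needs confirming.

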## Discussion

Despite their widespread use in the congestive heart failure, the evidence for intravenous loop diuretic administration is not as robust as many other treatments for heart failure (2). Loop diuretic agents work in a steep dose-response manner, in which dose intensification is often necessary to achieve a threshold concentration (ceiling) in invoking natriuresis (5). In AHF, this natriuretic threshold is increased, and the dose-response curves are shifted rightward in patients with concomitant kidney dysfunction (5), of which AHF accounts for 10 to 40% (16, 17). Although it has been established that a higher dose and a timely adjustment in the early stage of congestion should be implemented, there is still a need to determine the optimal dosing and timing strategy to overcome this diuretic resistance. The DOSE trial (3) demonstrated that a high loop diuretic strategy resulted in better decongestion (dyspnea improvement, weight change, and net fluid loss). However, this favorable effect was not investigated in the kidney dysfunction subgroup. Many trials have addressed the use of diuretics in patients with AHF and with kidney dysfunction. When the CARRESS-HF (18) trial compared ultrafiltration with a stepped approach to loop diuretic therapy in AHF patients with WRF, within 12 weeks before or 10 days after admission for heart failure and persistent congestion, renal failure developed in 15 and 18% of the stepped loop diuretic and ultrafiltration groups, respectively. This was despite the latter therapy being superior for preserving renal function 96 h after enrollment. However, WRF in AHF is a multifactorial condition, and an increase in serum creatinine does not always indicate a diuretic resistance. Evidence for appropriate diuretic therapy in patients with AHF with renal dysfunction and with diuretic resistance is still lacking. In 2019, the Heart Failure Association of the ESC suggested an aggressive diuretic treatment protocol (5). However, this has not been validated in AHF patients with renal dysfunction and with diuretic resistance.

Combination therapy offers many benefits in overcoming diuretic resistance. Most experts believe that it should not be initiated until the loop diuretic dose is up-titrated. However, no consensus has been reached regarding the time point for starting the add-on therapy. Although the combination diuretic treatment has recently gained more attention due to its physiologically synergistic action, its advantages may be outweighed by the substantial risk of electrolyte disturbances and a more severe WRF (2). Tolvaptan is promising for diuretic combination therapy. In the AQUAMARINE study (10), patients with AHF with renal dysfunction (defined as eGFR at admission 15–60 ml/min/1.73 m^2^) were randomized to tolvaptan add-on therapy or conventional diuretic treatment in the early stage of congestion (within 6 h after admission). This resulted in more diuresis and in better symptom relief without increasing the risk of WRF and electrolyte abnormalities. Recently, in a 3T trial (19), tolvaptan produced a higher cumulative urine output at 48 h and a lower risk of hyponatremia than the metolazone add-on therapy in patients with AHF and intravenous loop diuretics. The previous randomized trials and the current trial are summarized in Appendix 4. Overall, the DR-AHF trial is the first to evaluate the additive clinical value of treatment with tolvaptan in modern loop diuretic up-titrating therapy among patients with AHF and with verified diuretic resistance.

The DR-AHF trial has some limitations. First, as this is a single-center trial, some biases, such as selection bias, may not be entirely excluded. Moreover, this trial may be undersized to evaluate the prognostic impact of tolvaptan. Finally, this is an open-label trial in which the treatment of a doctor or the behavior of a patient can change.

In summary, the DR-AHF trial will demonstrate the efficacy of the timely intense loop diuretic monotherapy and tolvaptan combination treatment in the early stage of congestive heart failure with renal dysfunction and provide the clinical evidence of diuretic resistance.

